**Figure 6 F6:**
[figure not shown]
Diffusion MRI with region-of-interest-based deterministic tractography using TrackVis in sagittal **(A)** and coronal **(B)** view, rendered as described with MR data from the protocol pilot run (3T MAGNETOM Prisma, Brain Imaging Center Frankfurt) obtained from a healthy 32-year-old male test subject.

FEES are performed with an Olympus ENF-P4 laryngoscope attached to a camera (rpCam62, S/N) and a color monitor (17′ -TFT-EIZO, 1,500: 1). All examinations are videotaped. FEES procedures are performed by a neurologist and a speech-language pathologist, having several years of experience with the diagnostic tool. A standardized FEES protocol will be followed strictly. All swallowing trials are rated by an experienced speech pathologist according to the Penetration Aspiration Scale.

### Data Analysis

Descriptive statistics are used to present baseline characteristics. The 95% Confidence Intervals are calculated to verify the accuracy of our primary endpoint, the frequency of HOD occurrence in patients after lesions to the GMT. Differences between groups are tested by the independent-samples *t*-test for parametric data, Pearson's Chi-square test for categorical data, and the Mann–Whitney *U*-test for non-parametric data. Other statistical tests may be used where appropriate. For all analyses, the level of significance is set at *p* < 0.05. Diffusion MRI data analysis is outlined in detail in the Supplementary Material.

### Primary Endpoint

The primary endpoint of the study is the presence of radiological HOD on T2-weighted images at the time of follow-up 8 months after the index event. The presence of radiological HOD is reviewed and validated by two experts in the field, including at least one specialist in radiology with additional neuroradiology specialty, on the basis of the brain MRI with T2-weighted sequences. The radiological diagnosis of HOD is established in consensus if a new-appearing, circumscribed hyperintensity of the ION is present on T2-weighted or FLAIR imaging, optionally accompanied by hypertrophy of the ION (4, 8, 9).

### Secondary Endpoints

Secondary endpoint values are the radiological incidence of HOD at 4 months after the index event, recorded as the main target value. Further secondary endpoints are the presence of HOD-specific symptoms in the clinical exam at follow-up and the impact of HOD development on disability outcome (mRS). The PD-weighted images of all patients will be reviewed by three blinded raters with a specialization in neuroradiology and rated for their quality of HOD identification in comparison to simultaneously acquired T2-weighted images. The DTI images will be analyzed for each individual patient with respect to lesion location within the fiber tracts of the GMT, thinning of fiber tract volume, and quantitative imaging parameters such as mean diffusivity and fractional anisotropy and will be reviewed.

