### Sample Size

Due to the exploratory study design, an exact power calculation is not feasible. For the purpose of this study—the determination of HOD frequency after posterior fossa stroke—a maximum 10% deviation of actual disease incidence is considered within acceptable boundaries. Therefore, it is calculated that with a targeted study size of 100 study subjects, the 95% confidence limits are ≤ 10% different (absolutely) from the estimated cumulative frequency of HOD occurrence (e.g., if 30 cases are detected in *n* = 100 subjects, the 95% confidence limits are thus 0.21 and 0.40, as calculated by the Clopper-Pearson Exact method). A minimum of *n* = 100 patients is thus the targeted sample size. In addition, empirical data in the recruiting centers were assessed to approximate if sufficient patients matching inclusion criteria could be recruited. Based on yearly benchmark reports derived from the local quality assurance registry (https://www.gqhnet.de/leistungsbereiche/schlaganfall), ~6,000 ischemic and hemorrhagic stroke patients can be expected in the recruiting stroke centers per year (see below). A detailed evaluation of consecutive stroke patients from the Lausanne Stroke Registry showed that among 1,000 patients with first-ever stroke, 113 isolated brain stem infarctions, 17 isolated cerebellar infarctions, seven isolated brain stem hemorrhages, and nine isolated cerebellar hemorrhages can be expected (20). Other studies confirmed this distribution (21). Applying these numbers to the local prerequisites, an equivalent of 1,927 strokes in the brainstem and cerebellum in the 2-year study period can be estimated for the recruiting centers. Additionally, the study templates with the regions of interest were applied on 40 consecutive brainstem and cerebellar strokes in a pilot run in 2018, which showed that 35% of strokes had a general topo-anatomical relation to the GMT. Thus, in a 2-year period, 674 stroke patients with lesions affecting the region of interest can be expected in the recruiting centers. However, strict application of exclusion criteria showed that only a smaller portion of those patients could have been recruited, especially due to a lack of MR-feasibility, missing patient consent, and progressed disability due to the index stroke and advanced patient age (reflected in mRS > 4). Moreover, the SARS-Covid-19 pandemic unforeseeably complicates recruitment. Hence, the targeted number of patients to include in this study is *n* = 100, leaving a necessarily large scope for expected recruitment failures and patient exclusions. Based on these 100 patients, the proportion of patients developing HOD as well as the timeline of HOD development will be determined.

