### Inclusion and Exclusion Criteria

Patients are eligible for this study if they are older than 18 years and present in the recruiting centers with an intracerebral hemorrhage or cerebral infarction in the brainstem or the cerebellum not older than 14 days with topo-anatomical relation to the GMT. The region of interest is evaluated on clinical MRI or CT and predefined by the study template (Figure 4). If there is a match of lesion localization and MRI template the patient will be asked by the respective study centers to participate in the study. If there is an agreement, baseline clinical data is anonymously recorded in the study database, and the patient is contacted for follow-up (Figure 3).

Written informed consent is mandatory for recruitment. Patients are excluded from the study if explicit consent to participate in the study cannot be given due to coma or lack of legal competence. Further exclusion criteria are visibility of new operative injury on MRI (e.g., after an occipital craniotomy), contraindications to perform MR-imaging (such as pacemakers, ferromagnetic materials in the body, and claustrophobia), age under 18 years, and a modified Rankin Scale (mRS) of more than four points, which precludes transportation.

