### Study Outcomes

All patients are asked to undergo follow-up MR-imaging done at the Brain Imaging Center (BIC) of the Goethe University Frankfurt. Furthermore, at the time of study visits, a clinical neurological examination is performed by a study physician following a study exam catalog. The symptoms of a rhythmic PT, pendular nystagmus, and Holmes tremor of the upper limbs are specifically evaluated by a physician with experience in the field. A complete neurological exam is performed, including gait testing. The individual disability outcome is measured by the modified Rankin Scale (mRS) during each study visit. If PT is encountered, the patient is offered an evaluation of dysphagia by a speech-language pathologist, including optional FEES.

MRI examinations are performed on a 3T whole-body MRI scanner (MAGNETOM Prisma, Siemens Healthineers, Erlangen, Germany) using a body transmit and a 20-channel phased-array head/neck receive coil (Siemens Healthineers, Erlangen, Germany). As an anatomical reference, a T1-weighted data set with whole-brain coverage and an isotropic resolution of 1 mm are acquired using a 3D magnetization-prepared rapid-gradient-echo imaging (MP-RAGE) sequence (22). PD-weighted images, acquired with a long repetition time (TR) and a relatively short echo time (TE), are compared to both T2-weighted and fluid-attenuated inversion recovery (FLAIR) images. For best detection sensitivity of radiological HOD, an infratentorial axial T2-weighted sequence of the brainstem is included as a gold standard with the following parameters: matrix size 448 × 358, FOV 240 × 240 mm^2^, TE 116 ms, TR 4,400 ms, refocusing angle 130°, 20 axial slices, slice thickness 2 mm, and slice gap 0.2 mm. PD- and T2-weighted images are recorded simultaneously via a double-echo turbo spin echo sequence (TE 12 and 96 ms) with the following parameters: matrix size 384 × 384, FOV 240 × 240 mm^2^, TR 4,500 ms, refocusing angle 130°, 25 axial slices, slice thickness 2 mm, and slice gap 0.5 mm. In correspondence with the local clinical routine protocol, FLAIR images covering the entire brain are acquired with a matrix size of 320 × 224, FOV 220 × 193 mm^2^, TR 8,500 ms, TE 81 ms, TI (inversion time) 2,440 ms, refocusing angle 150°, 30 axial slices, slice thickness 4 mm, and slice gap 0.4 mm.

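### The only group tests the article names are unadjusted, so severity of the index stroke can be read as an effect of HOD on disability

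*Protocol article*

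**What the plan says.** The Secondary Endpoints section of the protocol article includes "the impact of HOD development on disability outcome (mRS"). On measurement, Study Outcomes states: "The individual disability outcome is measured by the modified Rankin Scale (mRS) during each study visit". Under Design, the visits fall at 4 and 8 months.

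At entry, one exclusion criterion is "a modified Rankin Scale (mRS) of more than four points, which precludes transportation". The same section says that "baseline clinical data is anonymously recorded in the study database", without listing the items.

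On method, Data Analysis begins "Differences between groups are tested by the independent-samples" t-test for parametric data, then gives Pearson's chi-square for categorical data and the Mann-Whitney U-test for non-parametric data. It adds: "Other statistical tests may be used where appropriate". The threshold is general: "For all analyses, the level of significance is set at" 0.05. The article names no regression model, covariate, stratification or change-from-baseline analysis for mRS.

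The Discussion says the recruitment template is deliberately generous, so lesions that touch the Guillain-Mollaret triangle only slightly also qualify. Anticipated Outcomes and Limitations expects a mixed cohort, with no randomisation or matching on stroke type or location.

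**The concern.** HOD is not assigned; it follows from the lesion. The Discussion plans to examine whether involvement of the dentate nucleus, central tegmental tract or red nucleus raises the risk of HOD. The Introduction reports that HOD frequency after posterior fossa surgery varied with approach and dentate injury. Site and extent of the lesion can also determine how disabled a patient is at 8 months. A crude comparison of mRS between patients with and without HOD then mixes any consequence of HOD with the consequence of the original stroke.

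The Discussion asks whether HOD matters to patients or is mainly a radiological finding, and the mRS comparison is one of the results that bear on this. It also warns that HOD symptoms can be wrongly blamed on the first stroke. An unadjusted comparison carries the opposite risk, that disability from the first stroke is credited to HOD. The stated limitations do not mention it.

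**Working it through.** **Inputs from the article.** Target of 100 patients (Sample Size). Anticipated HOD frequency of 20% at 8 months (Discussion), hence 20 versus 80. Significance level 0.05, taken as two-sided because sidedness is not stated. Entry mRS limited to 0 to 4 by the exclusion criterion.

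**Assumed inputs (the article gives neither).** The gap *d* in entry severity between HOD and non-HOD patients, in SD units, and the correlation *r* between entry and 8-month mRS. The true effect of HOD on mRS is set to zero.

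**The plan's own figure.** The article gives no figure for the mRS comparison. Its only precision figure, the exact interval for 30 of 100, recomputes to 0.2124 to 0.3998, matching the stated 0.21 and 0.40. The present point does not depend on it.

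**Step 1, hand approximation.** With no HOD effect, the entry gap carries forward as a follow-up gap of about *r* × *d* SD. The expected test statistic is *r* × *d* × √(20 × 80 / 100) = *r* × *d* × 4, and the rejection rate is about P(Z > 1.96 − 4*rd*).
- *r* = 0.5, *d* = 0.5: 4*rd* = 1.00, so P(Z > 0.96) ≈ 17%.
- *r* = 0.7, *d* = 0.5: 4*rd* = 1.40, so P(Z > 0.56) ≈ 29%.
- *r* = 0.7, *d* = 0.8: 4*rd* = 2.24, so P(Z > −0.28) ≈ 61%.

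This treats the scale as continuous. Grouping into mRS categories lowers the rates somewhat.

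**Step 2, simulation A.** Ordinal scores from latent normals, 4,000 trials per setting, 20 versus 80. Each cell shows Mann-Whitney, then rank ANCOVA on entry mRS.

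| Entry gap | r = 0.5 | r = 0.7 |
|---|---|---|
| 0.3 SD | 8.4%; 4.9% | 12.2%; 5.6% |
| 0.5 SD | 15.7%; 5.2% | 26.9%; 6.0% |
| 0.8 SD | 32.9%; 5.5% | 55.3%; 5.7% |

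**Step 3, simulation B.** Latent entry SD of 1.2 mRS points, entry score rounded and limited to 0 to 4, entry-to-follow-up coefficient 0.5 or 0.7, 2,000 trials per setting, 20 versus 80. Each cell shows Mann-Whitney, then a linear model adjusted for entry mRS.

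| Entry gap | coefficient 0.5 | coefficient 0.7 |
|---|---|---|
| 0 | 4.2%; 4.6% | 4.4%; 4.4% |
| 0.25 points (0.25/1.2 = 0.21 SD) | 6.0%; 5.4% | 8.6%; 4.8% |
| 0.5 points (0.5/1.2 = 0.42 SD) | 10.2%; 5.4% | 18.8%; 5.1% |
| 1.0 point (1.0/1.2 = 0.83 SD) | 31.2%; 5.8% | 51.9%; 7.0% |

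A gap of 0.5 points at entry produced a spurious follow-up difference of 0.20 to 0.30 mRS points. With 30 versus 70 patients, the same gap gave 12.6% to 21.6% unadjusted and about 5% adjusted.

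**Step 4, limit of the adjustment.** Steps 2 and 3 route all confounding through entry mRS, so adjusting for it must succeed. If lesion location also affects recovery directly, it does not. With *r* = 0.7, an entry gap of 0.3 SD and a further location effect of 0.2 or 0.35 SD (assumed), the entry-adjusted test rejected in about 18% and 42% of trials.

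**The case against.** The strongest reply is that the article does not assign any test to mRS. Data Analysis is a generic list by data type, it leaves other tests open, and covariates for a secondary endpoint of an exploratory cohort are often set out in a fuller protocol or analysis plan that is not shown here. This stands as far as it goes. A reader might infer that an unadjusted Mann-Whitney test of mRS is fixed, and the text does not support that. What remains is that a causally worded endpoint sits beside a list of methods, none of which can answer it. The open clause commits to no adjustment and leaves the choice until the data are seen.

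Three further inferences go too far:

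- **That stroke severity will be reported as an HOD effect.** This happens only if severity differs between the groups. The article has no data on that and calls the influence of lesion location on HOD unknown.
- **That entry mRS is on file for everyone.** The exclusion above 4 requires a judgement at entry, but the article does not say that the graded score is stored.
- **That adjusting for entry mRS removes the problem.** Step 4 of the working shows it need not.

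It is also fair to say that clinical relevance is judged mainly through palatal tremor, nystagmus and Holmes tremor, with mRS as one further item, and that the article already warns against generalising its findings.

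**Conclusion.** The point holds in a conditional form. The methods named are unadjusted and the groups are formed by the lesion itself, so index-stroke severity can confound the mRS comparison and be taken for an effect of HOD. For an entry gap of about 0.4 to 0.8 SD, the false-positive rate of an unadjusted Mann-Whitney test is roughly 10% to 55% instead of 5%. For a gap near 0.2 SD it is 6% to 9%, and with no gap the test is valid. The range rests on the assumed gap, the assumed entry-to-follow-up relation and the 20-to-80 split. It shows how large the problem could be and does not forecast this cohort.

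Adjustment for entry mRS is a clear improvement but only a partial one, so the result should be described as an association. The matter concerns one secondary endpoint; the HOD frequency is untouched.

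**What to change.** - **Main analysis.** Compare 8-month mRS by HOD status with proportional-odds regression or rank ANCOVA, adjusted for entry mRS and for stroke type (ischaemic or haemorrhagic). First confirm that the graded entry score, and not only the eligibility decision, is stored.
- **Sensitivity analysis.** Add lesion location as a covariate, as coarsely as about 20 HOD cases allow.
- **Wording.** Replace the term impact with association, and state that residual confounding by lesion site and extent remains.
- **Use of 4-month mRS.** Do not adjust for it in patients who already have HOD at 4 months. HOD may by then have changed that score, and a real effect could be adjusted away; the Discussion concedes that onset before or between visits cannot be distinguished. If such an analysis is wanted, restrict it to HOD that is new between 4 and 8 months.

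Cost: a few sentences of analysis text and one or two degrees of freedom for the main covariates. No new visit or measurement is needed if the entry score is stored; if it is not, one database field has to be added.

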As a secondary study goal, quantitative imaging data acquired from the study cohort is utilized to provide insight into the complex brainstem connectivity. It can be assumed that the dentato-thalamo-cortical pathways behind HOD development are involved in other higher brain functions as well, as observed in the cerebellar mutism syndrome after posterior fossa surgery (3). Prior studies already applied structural and diffusion MRI data on the ION complex, and successfully tracked connections of the ventrolateral (parvocellular) subregions of the RN to the ION (24). The DTI fiber tractography is thus promising to illustrate the chronological course of fiber tract degeneration in HOD and associate the anatomical lesions from routine T2-weighted MR images to the respective fiber tract injury. Hereby, lesion areas most vulnerable for HOD development can be identified and a comparison of fiber tract volumes between symptomatic and asymptomatic HOD could be undertaken.

The HOD is not a common radiological diagnosis, and changes in conventional T2-weighted images may often be too subtle for a confident diagnosis. This study aims to provide the clinical radiologist with a more sensitive and specific sequence to confirm the suspicion of HOD: double-echo PD-weighted images with long TR are available on most clinical MR-scanners and are hypothesized to generate more contrast in the brainstem, allowing for a more certain and hereby more common diagnosis.

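### The PD images get a comparative quality rating against the T2 echo of the same scan, under an unnamed blind; this does not by itself give the detection and false-positive rates that the stated aim needs

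*Protocol article*

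**What the plan says.** The Secondary Endpoints section has the PD-weighted images of every patient "reviewed by three blinded raters with a specialization in neuroradiology and rated for their quality of HOD identification". The yardstick is the T2 echo of the same scan: the images are "rated for their quality of HOD identification in comparison to simultaneously acquired T2-weighted images". It does not say what the blind covers.

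The Study Outcomes section explains where the two image sets come from: "PD- and T2-weighted images are recorded simultaneously via a double-echo turbo spin echo sequence", with echo times of 12 and 96 ms. They therefore show the same patient, scan and olives. A separate T2 acquisition serves as the standard: "an infratentorial axial T2-weighted sequence of the brainstem is included as a gold standard".

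The Primary Endpoint section defines the diagnosis without PD. It is "established in consensus if a new-appearing, circumscribed hyperintensity of the ION is present on T2-weighted or FLAIR imaging", and two experts make the call.

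On purpose, the Introduction hypothesises that double-echo imaging detects HOD better than conventional T2. The Objective and Design sections speak of comparing detectability. The Discussion goes further: "This study aims to provide the clinical radiologist with a more sensitive and specific sequence to confirm the suspicion of HOD".

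**The concern.** Whether one sequence detects a lesion better than another is a question about calls: how often each finds HOD when it is there, and how often each reports HOD when it is not. The measure named in the article is a quality rating of one sequence relative to the other.

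Two things follow. First, a rater who has both echoes in view can let a signal on one direct attention on the other, so the rating of PD is no longer a reading of PD alone. Second, a score for how well HOD is identified has no obvious content where there is no HOD, so it does not by itself show how often PD would raise a false alarm.

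At stake is one secondary target of the study. The PD data would be collected in full, yet the analysis might support only a statement of preference between two images.

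**Working it through.** **The plan's own figure.** The only precision figure in the article is in the Sample Size section: exact 95% limits of 0.21 and 0.40 for 30 cases in 100. The Clopper-Pearson limits are 0.2124 and 0.3998, so it reproduces. It concerns HOD frequency. The article gives no size or precision for the PD/T2 comparison, so this point has no stated number to test. The check is mainly a reading of the sections against each other.

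**Aim against measure.**

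| Section | What is sought or fixed |
|---|---|
| Introduction, Objective, Design | better detection or detectability of HOD |
| Discussion | gain in sensitivity and in specificity |
| Secondary Endpoints | quality rating of PD relative to the T2 echo |
| Primary Endpoint | reference diagnosis on T2 or FLAIR only |

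**What the aim needs.** The target size is 100 (Sample Size) and the expected HOD frequency at 8 months is 20% (Discussion).

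- Expected with HOD: 100 × 0.20 = 20.
- Expected without HOD: 100 − 20 = 80.
- Sensitivity of a sequence = positive calls on it among the 20, divided by 20.
- Specificity = negative calls on it among the 80, divided by 80.

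Both need a present/absent call for each sequence. The article names no such call in the PD/T2 comparison.

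**What a shared view could do (assumed figures only).** Let *s* be the detection rate of PD read alone, and *c* the share of PD misses that the rater recovers because T2 pointed to them. If T2 is scored alone, apparent PD detection is *s* + *c*(1 − *s*):

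| *s* | *c* = 0 | *c* = 0.5 | *c* = 1 |
|---|---|---|---|
| 0.60 | 0.60 | 0.80 | 1.00 |
| 0.75 | 0.75 | 0.875 | 1.00 |
| 0.90 | 0.90 | 0.95 | 1.00 |

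If help runs fully both ways, the two sequences converge. With PD at 0.90, T2 at 0.60 and independent misses, each appears to detect 1 − 0.1 × 0.4 = 0.96. A true difference of 30 points then shows as zero. So a joint reading may inflate PD, leave it unchanged, or hide a real advantage of either sequence. The document gives none of the inputs needed to say which.

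**The reference standard.** HOD is defined on T2 or FLAIR, so a signal visible only on PD cannot count as HOD. That works against PD, on different cases from those that carry-over affects. The two effects cannot be assumed to cancel.

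**The case against.** The case on the other side is strong in several places.

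- **A broken blind.** A reader might infer that the article promises a blind to the other sequence and then breaks it. It makes no such promise. Blinding to clinical findings, lesion side or the consensus diagnosis fits a comparative rating, so there is no contradiction. This stands.
- **Side-by-side reading.** This is the natural reading but is not stated. Separate reads compared in the analysis would also fit the sentence, and the word for simultaneity describes acquisition. This stands as a limit on certainty.
- **A calculated gain for PD.** A reader might argue that two sequences that each detect 80%, with independent misses, give PD an apparent 1 − 0.2 × 0.2 = 96%, a false gain of 16 points. The documents do not support this. If T2 is read with PD in view it also reaches 96%, and the difference is 0.96 − 0.96 = 0. Misses on two echoes of one acquisition may also be strongly correlated, which shrinks the gain.
- **False positives.** The images of all patients are reviewed and the rating scale is not given, so nobody can say that false positives go unrecorded. What can be said is that the named measure does not by itself supply them.
- **Condensation.** An article may leave session spacing and scoring forms to a fuller document. But this section does fix the number and specialty of the raters, a blind, a comparator and a measure. The point is about the measure it fixes, not about detail left out.
- **Weight.** This is a secondary target of an exploratory study. The sensitivity and specificity wording is in the Discussion only, although the Introduction, Objective and Design also aim at detection. This keeps the point modest but does not remove it.

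**Conclusion.** The point holds in a limited form. The rating described in the Secondary Endpoints section is comparative, is naturally read as made with both echoes in view, and sits under a blind whose content is not named. It does not by itself give independent detection and false-positive rates per sequence, which the aim requires.

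No size or direction of bias can be put on it. It should not be read as evidence that PD will be favoured. The conclusion on independence rests on the natural reading of the sentence and falls away if separate reads were already intended. The mismatch between a quality score and a detection aim remains unless the score includes a present/absent call.

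The primary endpoint does not depend on the PD reads. This is a cheap improvement, not a fault that endangers the study.

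**What to change.** In the Secondary Endpoints section:

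1. State that the three raters are blinded to clinical findings and to the consensus diagnosis.
2. Have each rater read PD and T2 of a patient separately, de-identified, in random order and in different sessions.
3. At each read, record HOD present or absent for each olive, with a confidence score.
4. Compare the paired calls in all patients, including those without HOD.
5. Keep the side-by-side quality rating as a later descriptive step.

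The same three raters and images serve. The cost is one extra reading session per rater.

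Three limits remain. A rater will still recognise the sequence from its contrast; that is inherent and this change does not cure it. Rates will still be relative to a T2/FLAIR diagnosis, so PD-only findings should be shown as discordant pairs. With about 20 HOD cases precision stays low: a rater who found 15 of 20 would have exact 95% limits of 0.51 to 0.91, so the comparison remains exploratory.

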Advanced imaging techniques have been sporadically applied in HOD patients in this regard to visualize fiber tracts associated with HOD development. Diffusion tensor imaging (DTI) with tractography can be used to analyze the change in fiber tract volume following injury in the GMT (14–16). The use of this method systematically to investigate the HOD development and more precisely understand the injury to brainstem connectivity is promising beyond merely pinpointing down a lesion to an anatomic localization on MRI or in *ex-vivo* pathological studies. Furthermore, the distinction between affected and unaffected patients allows us to identify contributing factors to HOD occurrence. To our knowledge, no such prospective acquisition of DTI fiber tracking data in HOD patients has been described in the literature so far.

Moreover, proton density (PD)-weighted imaging was shown to be well-suited for detecting infratentorial lesions in the posterior fossa, yielding good contrast between cerebrospinal fluid (CSF) and brainstem lesions (17, 18). Transferring this to HOD imaging, it can be hypothesized that double-echo sequences (including T2- and PD-weighted datasets) are superior in the detection of HOD compared to conventional T2-weighted imaging and provide an improved detectability of the underlying lesion to the GMT.

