## Methods and Analysis

### Design

This is a prospective multicenter study conducted in Hesse, Germany, with a 2-year-recruitment period from March 2020 to February 2022. Patients with cerebral infarctions and cerebral hemorrhages in the brainstem and cerebellum with a topo-anatomical relation to the GMT are included and followed prospectively for 8 months (Figure 3). The patients are exclusively selected based on a pre-defined digital MRI template covering the region of interest (Figure 4). During this period, two clinical neurological examinations and two follow-up MRI scans of the brain are performed at 4 and 8 months after the index event, respectively. Three major targets are defined: (1) determining the risk of HOD development for patients with ischemic or hemorrhagic lesions within the GMT, (2) defining the timeline of radiological and clinical onset of HOD, and (3) defining a real-world pattern of the clinical syndrome of HOD in clinical follow-up examinations. Three secondary targets are defined: (a) the acquisition of an additional MRI DTI protocol with fiber tractography to demonstrate the chronological decrease in fiber tract volume over time in parallel to the development of clinical symptoms and conventional radiological findings, (b) the acquisition of MRI double-echo PD-/T2-weighted images to analyze the best detectability of radiological HOD in comparison to conventional T2-weighted sequences, and (c) the assessment of PT associated dysphagia by a follow-up examination by speech therapists with Fiberoptic endoscopic evaluation of swallowing (FEES) (Figure 5) (19). The study does not include medication or the admission of computed tomography (CT) or other sources of radiation at any point.

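### The rater endpoint sets PD against the T2 echo of its own sequence, so as written it cannot support the stated target of double-echo PD/T2 against conventional T2

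*Protocol article*

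**What the plan says.** The protocol article describes the PD/T2 comparison in several places.

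- **Introduction** (paragraph on PD-weighted imaging), the hypothesis: "double-echo sequences (including T2- and PD-weighted datasets) are superior in the detection of HOD compared to conventional T2-weighted imaging".
- **Objective**: a looser aim, to compare how well HOD can be detected on T2 and on PD data. It does not say which T2.
- **Design, secondary target (b)**: "the acquisition of MRI double-echo PD-/T2-weighted images to analyze the best detectability of radiological HOD in comparison to conventional T2-weighted sequences".
- **Study Outcomes**: PD is to be compared with T2 and with FLAIR, again without saying which T2. The section then describes two separate T2 series. For the first, "an infratentorial axial T2-weighted sequence of the brainstem is included as a gold standard" (TE 116 ms). The second is one half of the double-echo acquisition: "PD- and T2-weighted images are recorded simultaneously via a double-echo turbo spin echo sequence (TE 12 and 96 ms".
- **Secondary Endpoints**, the operative text: "The PD-weighted images of all patients will be reviewed by three blinded raters with a specialization in neuroradiology" and these images are "rated for their quality of HOD identification in comparison to simultaneously acquired T2-weighted images".

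The Abstract lists the best imaging regimen for identifying HOD among the secondary endpoints. The Discussion hopes to give radiologists a sequence more sensitive and specific than conventional T2. Under Primary Endpoint, HOD is diagnosed by consensus of two experts on T2-weighted or FLAIR images.

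**The concern.** The T2 echo of the double-echo sequence changes sides. In the hypothesis and in target (b) it belongs to the method under test. In the rater endpoint it is the control. The separate dedicated T2, which the protocol includes for its detection sensitivity, is not named in the rater comparison at all.

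If the endpoint is carried out as written, a favourable result shows that raters prefer the first echo of one sequence to its second echo. The dedicated T2 could do better than both echoes and the endpoint would not reveal it. The aim of finding the best regimen, and the expectation in the Discussion that radiologists gain something over conventional T2, would then rest on a comparison that was never made.

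**Working it through.** There is no stated figure to reproduce: the protocol gives no sample size or precision for the rater comparison. The check is therefore of wording, with a short look at the printed scan parameters.

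**Step 1. Contrasts side by side**

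| Section | Method under test | Comparator |
|---|---|---|
| Introduction (hypothesis) | Double-echo, PD and T2 together | Conventional T2 |
| Objective | PD | T2, series not named |
| Design, target (b) | Double-echo PD/T2 | Conventional T2 |
| Study Outcomes | PD | T2 (series not named) and FLAIR |
| Secondary Endpoints | PD | Simultaneously acquired T2 |

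The Introduction and Design agree with each other. Secondary Endpoints differs from them in both columns. Study Outcomes is a third version, because it adds FLAIR. Objective is loose enough to be met by the rater endpoint.

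**Step 2. Which T2 is simultaneous?** Study Outcomes uses that description only for the double-echo pair. The natural reading of the endpoint is therefore TE 12 ms against TE 96 ms within one sequence. This is an inference. The word could loosely mean the same scan session, which would also admit the dedicated T2.

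**Step 3. Are the two T2 series interchangeable?** Inputs from Study Outcomes; FOV is 240 × 240 mm and slice thickness 2 mm for both.

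| | Dedicated T2 | Double-echo T2 |
|---|---|---|
| TE | 116 ms | 96 ms |
| TR | 4,400 ms | 4,500 ms |
| Matrix | 448 × 358 | 384 × 384 |
| Pixel size (FOV / matrix) | 240/448 = 0.536 mm by 240/358 = 0.670 mm | 240/384 = 0.625 mm in both directions |
| Pixel area | 0.536 × 0.670 = 0.359 mm² | 0.625² = 0.391 mm² |
| Slice gap | 0.2 mm | 0.5 mm |
| Share unsampled, gap / (thickness + gap) | 0.2/2.2 = 9.1% | 0.5/2.5 = 20% |

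The in-plane difference is small, and the double-echo series is the finer one in one direction. TE and gap differ more. The series are not the same image, so a result against one does not carry over to the other.

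**Step 4. What these figures do not show.** PD and its T2 echo come from the same acquisition and share its matrix and its 0.5 mm gap. The 20% applies equally to both sides of the endpoint's comparison, so it gives PD no advantage there.

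**Step 5. The reference standard.** HOD is diagnosed on T2 or FLAIR, and the dedicated T2 is called the gold standard. Against such a reference, an olive seen as abnormal only on PD counts as a false positive. The most PD can do is agree with the reference, so adding the dedicated T2 as a comparator does not by itself allow a claim of higher sensitivity or specificity for PD.

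**The case against.** The strongest reply is that this is a gap in wording. The Objective asks for T2 against PD, and the endpoint delivers that. PD against the T2 echo of the same acquisition is a sound way to isolate the effect of PD weighting, because geometry is matched. A comparison with the dedicated T2 mixes contrast weighting with differences in TE, matrix and gap. All series are acquired, Study Outcomes already mentions a wider comparison, and the study calls itself exploratory.

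Much of this stands. The matched contrast is worth keeping, the Objective is served, and the data for target (b) will exist. What remains is that the endpoint's comparator and the target's comparator are both stated and do not agree. The wider comparison in Study Outcomes names no T2 series and does not reappear in the rater endpoint. If the same-session meaning of simultaneous is allowed, the comparator is ambiguous and still has to be named.

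A reader might infer that the larger slice gap or different matrix makes the comparator weak and so flatters PD. The documents do not support this, because PD shares both. A reader might also infer that the study cannot test target (b). It can, since the images are acquired. Only the endpoint as written does not.

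Reading order, separate sessions and confidence grading are details that an article commonly leaves to the full protocol, and their absence is not part of this point.

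**Conclusion.** The point holds as a conflict between stated comparisons. Followed as written, the rater endpoint answers whether PD is rated better than the T2 echo of its own sequence. It cannot support a claim that double-echo imaging detects HOD better than conventional T2, which is what the hypothesis and target (b) ask.

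The reach is limited to one secondary imaging endpoint in an exploratory study. The primary endpoint and the target of 100 patients are unaffected. No size or direction of bias can be derived from the documents, and none is claimed.

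The conclusion rests on two assumptions: that simultaneous means the double-echo pair, which the wording of Study Outcomes strongly suggests, and that conventional T2 under Design means the dedicated infratentorial T2, the only other T2-weighted series described apart from FLAIR. The protocol makes neither identification explicit.

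**What to change.** Under Secondary Endpoints:

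1. Add the dedicated infratentorial T2 as a named comparator, read by the same three blinded raters.
2. Keep PD against its own T2 echo as the matched-geometry contrast.
3. State whether the method under test is PD alone or the PD/T2 pair.
4. For each series, report HOD yes/no as paired results, including how many patients are positive on one series only in each direction, with inter-rater agreement. Do not claim higher sensitivity or specificity for PD against a T2-based reference, and adjust the expectation in the Discussion to match.

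Then align the Introduction, Design and Study Outcomes with this wording, including whether FLAIR is a comparator.

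**Cost.** No new scans or raters. With 100 patients, reading the dedicated T2 adds about 100 readings per rater per visit. Reading the PD/T2 pair jointly as well adds another 100, so about 200. If both the 4- and 8-month scans are read, the totals double to 200 to 400 per rater. The added contrast compares whole sequences, which differ in TE, matrix and gap, and should be reported as such and not as the effect of PD weighting alone.
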